#### Additional measures

Participants in the intervention group will be administered the following self-report measures at each apprenticeship occasion in order to examine changes in self-efficacy and stress over the course of the apprenticeship: A generic one-item, 10-point Likert scale of subjective stress immediately before attending treatment sessions (Instruction: “*Notice how you’re feeling right now*. *Indicate on the scale below how much stress you’re experiencing in this moment*”); four items from the session management dimension of the Counselor Activity Self-Efficacy Scales, CASES [50] (see description of the measure above), and a generic one-item, 10-point Likert scale of confidence in the therapist role (Instruction: “*Indicate the alternative that you feel represents you best right now in your development as a therapist*: *How confident do you feel in the role as a therapist*?”).

At baseline, a battery of questionnaires will be administered to participants in both conditions in order to examine predictors of FIS across conditions and potential moderators to the impact of the apprenticeship training. Personality will be assessed with the NEO Five-Factor Inventory, NEO-FFI [57], a 60-item measure of the five basic personality factors Neuroticism, Extraversion, Openness, Agreeableness, and Conscientiousness. Items are scored on a 5-point Likert scale, from 1 (*strongly disagree*) to 5 (*strongly* agree). The NEO-FFI is a reliable, valid, and widely used personality measure [e.g., 58].

Self-assessed social skills will be assessed with the Social Skills Inventory, SSI [59], a 90-item measure of three types of verbal and non-verbal communication skills: expressivity, sensitivity, and control over communication. Items are scored on a 5-point Likert scale from 1 (*not at all like me*) to 5 (*exactly like me*). A sample item is “*I am often told that I am a sensitive*, *understanding person*”. The instrument has been reported to have good psychometric properties including test-retest reliability and convergent and discriminant validity [60].

Interpersonal functioning will be assessed with the Inventory of Interpersonal Problems, IIP-64 [47, 61], a 64-item measure of maladaptive relationship behavior. Items are scored on a 5-point Likert scale, from 0 (*not at all*) to 4 (*extremely*). Eight subscales correspond to octants in the Interpersonal Circumplex (domineering/controlling, vindictive/self-centered, cold/distant, socially inhibited, non-assertive, overly accommodating, self-sacrificing, and intrusive/needy). The inventory is widely used both in treatment and research and its validity and reliability are well documented [e.g., 62, 63].

Adult attachment quality will be assessed with the Experiences in Close Relationships–Short form, ECR-S [64]. A total of 12 items are scored on a 7-point Likert scale, from 1 (*disagree strongly*) to 7 (*agree strongly*). A sample item is “*I find it difficult to allow myself to depend on romantic partners*”. Like the original, 36-item version of ECR, the psychometric properties of ECR-S have been shown to be sound [64].

Capacity for mentalization will be assessed with the Mentalization Scale, MentS [65]. A total of 24 items are scored on a 5-point Likert scale, from 1 (*completely incorrect*) to 5 (*completely correct*). Three dimensions are assessed: self-related mentalization, other-related mentalization, and motivation to mentalize. A sample item is “*Often I cannot explain*, *even to myself*, *why I did something*”. The MentS is a relatively new inventory whose consistency, reliability, and validity has been reported to be adequate to good [65, 66].

Psychosocial functioning will be assessed with the Identity and Intimacy subscales (28 items) of the Measures of Psychosocial Development MPD [67]. The full, 112-item instrument assesses the positive and negative ends of each of Erikson’s eight psychosocial stages as well as the resolution of these stages. Items are scored on a 5-point Likert scale from 1 (*not at all like* me) to 5 (*very much like* me). Adequate to strong construct validity, test-retest and internal consistency was reported in the MPD manual [67].

The quality of the group climate in students’ practicum groups, which all students attend as part of training-as-usual, will be assessed with the Group Climate Questionnaire—Short form, GCQ [68]. A total of 12 items are scored on a 7-point Likert scale, from 1 (*not at all*) to 7 (*extremely*). Three subscales are assessed: Engagement, Avoidance, and Conflict. The GCQ is the most frequently used group process measure in the group psychotherapy literature and satisfactory reliability of the measure has been reported in several studies [e.g., 69, 70].

To examine and control for the potential impact of stress/heightened activation on performance on the FIS, students will be asked to complete a generic one-item measure of subjective stress (similar to the one administered at each apprenticeship occasion, see Secondary outcomes), immediately before the FIS test. Following the FIS test participants are asked to rate, on 10-point Likert scales, how much they feel that what they said would be helpful to the patient and to what degree they feel their responses represent their skills at a therapist, considering their current educational stage.

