Bandura [34] theorized that one’s self-efficacy in a given area is influenced by four sources: *Mastery experiences* of being able to succeed in performing behaviors or tasks in that area, *vicarious experiences* of watching social role models similar to oneself perform such behaviors or tasks successfully, *verbal persuasion* in the form of positive feedback and encouragement from others, and one’s own level of *emotional arousal* while performing the task. Psychotherapy apprenticeships might work to improve psychotherapy students’ self-efficacy through all four sources. Most notably, the exposure to relatable therapist role models performing their craft in a real-life setting is likely to be a powerful vicarious experience. Moreover, in therapy sessions students can perform simple psychotherapy tasks (e.g., expressing warmth and positive regard for the patient, sharing their understanding of what the patient is experiencing, history-taking), thereby gaining mastery experiences. Any encouragement or positive feedback that therapists give to students following such experiences is a source of verbal persuasion that is directly linked that performance. Finally, repeated exposures to real-life therapy in the presence of a more experienced other may habituate psychotherapy students to the emotional challenges involved in working with individuals in distress, thereby decreasing their arousal and increasing their self-efficacy. We find this aspect particularly important in light of psychotherapy students’ high degree of worry about their abilities to perform therapy [35, 36] and novice therapists’ elevated anxiety levels in treatment sessions [13, 37], which is likely to draw their attention away from the unfolding interaction with the patient [35].

From the experienced therapists’ perspective, apprenticeship offers a way to transmit experience-based knowledge to a new generation of practitioners. It also provides an extra set of eyes and ears in the therapy room. Our own experience working with students is that their “naïve stance” can provide new, and sometimes surprising, perspectives on our own work. Moreover, we find students’ positive energy and enthusiasm for our craft refreshing and energizing.

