Does the addition of apprenticeship to training-as-usual increase psychology students’ Facilitative Interpersonal Skills (FIS) more than training-as-usual alone?Is the hypothesized impact of apprenticeship on FIS associated with an increase in self-efficacy and a decrease in stress over the course of the practicum?Is apprenticeship training beneficial to students’ levels of worry, rumination, and self-compassion?Are students’ FIS scores associated to their personality traits, interpersonal functioning, social skills, attachment security, capacities for mentalization, and the group climate of their training-as-usual practicum course, and do these variables moderate the hypothesized impact of apprenticeship on FIS?Are the hypothesized gains obtained through apprenticeship training maintained over a two-year period?What are the salient aspects of therapy sessions for first-year students, and what characterizes the learning process in apprenticeships?How does working together with student apprentices impact licensed therapists, and is apprenticeship a feasible training model in mental health care?

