### Statistics and data analyses

Quantitative outcomes will be analyzed using regression models in which post-intervention and follow-up scores will be predicted by condition, controlled for pre-intervention scores and other possible covariates. Longitudinal models will examine the development over time on the session-by-session stress and self-efficacy measures. Missing data will be handled with multiple implementation. Qualitative data will be thematically analyzed.

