## Discussion

This randomized controlled trial and qualitative investigation will explore the potential impact of applying an educational method widely practiced in other fields, the apprenticeship, to the training of future psychotherapists. We consider it to be a promising supplementary element to the traditional (e.g., coursework, clinical practice under supervision) as well as the newer (e.g., deliberate practice) methods of psychotherapist training. In their apprenticeships, students will be exposed to the complexity—and sometimes messiness and confusion—of psychotherapy as it is practiced in actual clinical settings. A variety of ways to respond to challenging interactions in therapy will be demonstrated by relatable role models. Importantly, students will have the opportunity to discuss and gain insight into what considerations lie behind these role models’ actions with their clients, as well as to try out their own therapeutic skills under close guidance. We expect this to be facilitative of students’ interpersonal skills, to increase their self-efficacy, decrease their performance anxiety and stress, and to advance their understanding of the practical psychological work. This would demonstrate a proof-of-concept by this study. We also expect it to be engaging and helpful for the experienced therapists to welcome student co-therapists into their therapy room.

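### The stated intent to control FIS for stress rated just before the test is not limited to the baseline rating; using post-randomisation ratings would stop the FIS models estimating the randomised total effect

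*Protocol article*

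**What the plan says.** **Purpose and timing of the item.** Additional measures describes a one-item stress rating, completed "immediately before the FIS test". Its stated purpose is "To examine and control for the potential impact of stress/heightened activation on performance on the FIS". Examining and controlling are both named.

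**Schedule.** Table 1 places the stress scale under outcome variables at baseline (-t1), post-intervention (t11) and two-year follow-up (t12), the same three occasions as the FIS. That row has no asterisk, so it covers both arms. A separate, asterisked row covers the session ratings (t1 to t10), collected in the intervention arm only. Allocation states that randomisation follows the baseline measures, so only the -t1 rating precedes it.

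**Expected effect on stress.** The Introduction expects repeated exposure to therapy to habituate students, "thereby decreasing their arousal and increasing their self-efficacy". Research question 2 asks: "Is the hypothesized impact of apprenticeship on FIS associated with an increase in self-efficacy and a decrease in stress over the course of the practicum". The Discussion expects apprenticeship "to increase their self-efficacy, decrease their performance anxiety and stress".

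**Analysis model.** Statistics and data analyses describes regressions of post-intervention and follow-up scores on condition, "controlled for pre-intervention scores and other possible covariates". Stress is not named there, and the other covariates are not restricted to baseline variables.

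**The concern.** Research question 1 asks whether adding apprenticeship raises FIS more than training-as-usual alone. Research question 5 asks whether gains last two years. Both concern the total effect of randomised condition, including any part that works by making students calmer.

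A stress rating at t11 or t12 is taken after randomisation and may itself have been changed by the intervention. With that rating in the FIS model, the condition coefficient compares students at equal stress. Any benefit carried by lower stress is then taken out of the estimate. Conditioning on the rating can also link condition to unmeasured causes that stress and test performance share, so the coefficient need not be a clean direct effect either.

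The protocol gives one scale two roles that conflict in the same model: an outcome expected to improve, and a nuisance to be controlled for in FIS performance. Because the covariate list is open, the choice between an adjusted and an unadjusted estimate could also be made after both have been seen.

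**Working it through.** **1. The plan's own figure.** Inputs from Sample size: d = 0.5, one-sided alpha .05, 80% power, 100 analysed, 120 recruited with 20% attrition allowed for.
- Normal approximation, 50 per arm: power = Φ(0.5 × √(50/2) − 1.645) = Φ(2.500 − 1.645) = 80.4%. With the t distribution it is 79.9%. The stated figure reproduces.
- 120 × 0.8 = 96, or 48 per arm: 78.4% (t distribution). This is the reference below. The step from 79.9% to 78.4% comes from the smaller number, not from the stress issue.

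**2. What adjustment does to the target.** Put FIS and stress in within-arm SD units. Let a be the fall in pre-test stress caused by apprenticeship, and b the FIS loss per SD of stress within arm. In a linear model:
- adjusted coefficient = total effect − a × b = 0.5 − ab;
- residual SD = √(1 − b²), the precision gained from the covariate;
- arm–stress r² = (a²/4) / (1 + a²/4);
- SE = √(1 − b²) × √(2/48) / √(1 − r²).

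The documents give neither a nor b. The ranges a = 0.2 to 0.5 and b = 0.1 to 0.4 are assumptions.

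**3. Results, 48 per arm, one-sided .05, t distribution.**

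| a | b | Removed (ab) | Adjusted d | SE | Power |
|---|---|---|---|---|---|
| not adjusted | – | 0 | 0.50 | 0.204 | 78.4% |
| 0 | 0.3 | 0 | 0.50 | 0.195 | 81.7% |
| 0.2 | 0.1 | 0.02 | 0.48 | 0.204 | 75.5% |
| 0.3 | 0.3 | 0.09 | 0.41 | 0.197 | 66.4% |
| 0.5 | 0.4 | 0.20 | 0.30 | 0.193 | 46.0% |

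Worked last row: 0.5 − 0.5 × 0.4 = 0.30. r² = 0.0625/1.0625 = 0.059. SE = √0.84 × √(2/48) / √0.941 = 0.193. Ratio = 0.30/0.193 = 1.556, giving 46.0%.

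So 4% to 40% of the assumed effect is removed (0.02/0.5 to 0.20/0.5).

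**4. Check by simulation.** With 50 per arm and 4,000 runs per setting, the unadjusted model recovered about 0.50 throughout. The adjusted model gave 0.405 at a = 0.3, b = 0.3 (expected 0.41) and 0.345 at a = 0.5, b = 0.3 (expected 0.35). At a = 0 it gave 0.499, so nothing was removed.

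**5. What is left out.** Adjustment for baseline FIS would raise power with or without stress in the model. Bias from unmeasured shared causes of stress and performance is not quantified.

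**The case against.** The strongest reply is that no sentence puts t11 or t12 stress into the primary FIS model. The purpose statement sits in a description of measures and names no model, time point or estimand. The analysis section never mentions stress. Acceptable readings fit the same words: adjusting for the baseline rating, examining stress as a correlate of FIS, or running a sensitivity or mediation analysis. A final covariate list is also normally left to a fuller document that is not shown. This stands in part. A reader might infer that the plan has already committed to conditioning its primary analysis on a mediator; the documents do not support that. But the point does not rest on a missing list. It rests on a stated intent to control, attached to an item repeated before later FIS tests, which nothing shown confines to baseline or to a secondary analysis.

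The second reply is that the mediator link is loose. Research question 2 speaks of stress during the practicum, which points mainly to the session ratings in the intervention arm. The Introduction's mechanism is habituation to working with people in distress, not to being tested. This also stands: the pre-FIS rating is a plausible marker of the pathway, not one the protocol names. It is, however, a similar item, the only stress measure available in both arms, and listed as an outcome. The argument needs only that apprenticeship may change it, and the Discussion expects performance anxiety and stress to fall.

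The third reply is that the size is wholly assumed. That is correct. If a = 0, adjustment costs nothing and slightly improves precision. If apprenticeship raised pre-test stress, the bias would run the other way.

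**Conclusion.** The concern holds as a conditional one. The protocol declares an intent to control FIS for stress rated just before the test and does not restrict it to the baseline rating. If t11 or t12 stress is used that way in the FIS models for research questions 1 and 5, the condition coefficient is no longer the randomised total effect, and under the protocol's own theory it shrinks toward zero. The loss is 0.02 to 0.20 SD of a 0.5 SD effect, with power at 96 analysed going from about 78% to between about 76% and 46%. This rests on the assumed ranges for a and b, a linear model and no unmeasured shared causes. It runs from trivial to large, and the documents cannot narrow it.

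It would go too far to say that the trial will lose part of its effect: the harmful model is allowed, not written. This should be fixed before analysis, but it does not undermine the design.

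**What to change.** Add one sentence to Statistics and data analyses: the post-intervention and two-year FIS models adjust only for variables measured before randomisation, namely baseline FIS and, if wanted, the -t1 stress rating. State also that t11 and t12 stress is analysed only as an outcome compared between arms, or in an analysis labelled as mediation (for research question 2) or sensitivity. Align the purpose statement in Additional measures with this.

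The cost is a few lines of text. The ratings are already scheduled, so no new data are needed, and the sample size does not change. The baseline rating can still be used for precision.

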#### Qualitative data

Written reflective logs will be completed by students in the intervention group immediately following each treatment session they attend. The logs serve the dual purpose of facilitating the learning process by encouraging students to reflect upon salient aspects of their apprenticeship experience, and of providing a session-by-session insight into the learning process. In the logs, students will be asked to describe and reflect upon their immediate experiences of participating in each particular treatment session. Students in the intervention group as well as therapist participants will be invited to participate in focus group interviews focusing on the overall experience and impact of the apprenticeship training. Each focus group will consist of four to seven students or therapists and a moderator. All interviews will be audio-recorded and transcribed verbatim.

### Procedures

#### Enrolment

Prospective student participants will be informed about the study and encouraged to volunteer in lectures at the university. Written, informed consent will be required for student participants and will be obtained by members of the research team prior to randomization. Therapist participants will be recruited by presenting the study to each of the various outpatient teams at the three clinics.

To facilitate recruitment, student participants in both conditions will be compensated with bus passes for the duration of the apprenticeship intervention. Control condition participants will be offered a workshop on interpersonal skills following their completion of the post-intervention measures. No data will be collected from this workshop; instead, it is intended as a compensation for the students’ participation.

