#### Primary outcome

The main outcome change from baseline in the Facilitative Interpersonal Skills (FIS) test [43], performed at baseline, post-intervention and two-year follow-up. It is a practical skills test in which a test person responds to video stimuli of actors portraying clients in various difficult or challenging moments in therapy. The situations ***are*** designed to represent behavior in the various areas of the Interpersonal Circumplex model [47], such as an angry and confrontational client or a quiet and withdrawn client. The test person is instructed to respond verbally to each particular situation, as if they themselves were that client’s therapist, in a way they believe might be helpful. Responses are video recorded and subsequently rated in accordance with the FIS manual [48] for the degree of interpersonal skills on a scale from 1 (*not characteristic*) to 5 (*extremely characteristic*). The FIS assesses eight interpersonal skills, namely 1. Verbal Fluency, 2. Hope and Positive Expectations, 3. Persuasiveness, 4. Emotional Expression, 5. Warmth, Acceptance, and Understanding, 6. Empathy, 7. Alliance Bond Capacity, and 8. Alliance Rupture-Repair Responsiveness. The overall mean score will be utilized in analyses.

The original FIS stimuli clips were translated into Norwegian language and re-recorded with student actors by authors of this study protocol. A preliminary validation study [49] found interrater agreement and internal consistency on the Norwegian FIS test to be excellent. In this trial, students in both conditions will be tested on six clips each at pre- and post-interventions and at two-year follow-up. At each measurement occasion clips are selected to represent a balanced and varied range of challenging clinical situations. Responses will be rated by psychology students trained in the FIS methodology and blind to treatment condition and time of assessment.

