#### Assessment

Baseline data (-*t*_1_) will be collected prior to randomization and consists of the FIS skills test, administered by members of the research team, as well as several self-report measures of secondary outcomes and potential correlates of the FIS. See above for details about measures and outcomes. Session-by-session self-reported stress- and self-efficacy measures as well as reflective log entries will be completed by students in the intervention group at each clinic and immediately before and after each treatment session they attend (*t*1 –*t*_10_). Following the 10-week apprenticeship period (*t*_11_), students in both conditions will complete the FIS-test at the university, using different stimulus clips from those that were used pre-intervention, as well as self-report measures of secondary outcomes. At this point in time, students in the intervention group as well as therapists will be invited to focus group interviews. Follow-up data (*t*_12_) will be collected from students in both conditions two years after the completion of the apprenticeship condition, and consist of the FIS test as well as self-reported secondary outcomes.

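### Only the control arm is offered an interpersonal-skills workshop before the two-year test, so the two-year comparison no longer isolates apprenticeship

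*Protocol article*

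**What the plan says.** Under Enrolment, the protocol article describes compensation for students randomised to control: "Control condition participants will be offered a workshop on interpersonal skills following their completion of the post-intervention measures". It continues: "No data will be collected from this workshop; instead, it is intended as a compensation for the students’ participation". No matching offer is described for the apprenticeship arm.

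Under Primary outcome, FIS is "performed at baseline, post-intervention and two-year follow-up". Under Assessment, the follow-up data "will be collected from students in both conditions two years after the completion of the apprenticeship condition, and consist of the FIS test"; the self-reported secondary outcomes are collected then too. Under Statistics and data analyses, "post-intervention and follow-up scores will be predicted by condition, controlled for pre-intervention scores and other possible covariates". The fifth research question in the Introduction asks: "Are the hypothesized gains obtained through apprenticeship training maintained over a two-year period"?

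Study design defines the randomised comparison as training-as-usual with and without apprenticeship. Strengths and limitations presents the design as isolating the contribution of apprenticeship as the one added component. That section does not mention the workshop.

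**The concern.** The workshop falls between the post-intervention assessment (t11) and the two-year assessment (t12). It goes to one randomised arm only, and its stated topic is the construct that the primary outcome measures. At t11 the arms differ by apprenticeship alone. At t12 they differ by apprenticeship in one arm and a workshop offer in the other.

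What is at stake is the meaning of the two-year estimate. A small t12 difference could arise because apprentices lost their gain, because controls were trained, or both. The same applies to t12 self-efficacy on the adapted CASES, which asks about confidence in helping skills. The article plans no data from the workshop, which read literally excludes even an attendance list, so exposure in the control arm could not be described afterwards.

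**Working it through.** **1. What differs between the arms at each assessment**

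| Assessment | Intervention arm | Control arm | FIS difference estimates |
|---|---|---|---|
| t11 | usual training + apprenticeship | usual training | apprenticeship effect |
| t12 | usual training + apprenticeship | usual training + workshop offer | apprenticeship effect remaining at two years, minus average workshop effect remaining |

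The t11 row matches the comparison defined under Study design. The t12 row does not.

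**2. The plan's own sample size.** Inputs from the Sample size section: d = 0.5, one-sided alpha .05, power 80%, 1:1 allocation.

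n per arm = 2 × (1.645 + 0.842)² / 0.5² = 49.5, rounded up to 50, or 100 in total. This reproduces the stated figure; the t-test power at 50 per arm is 0.799.

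With 120 enrolled and the planned 20% attrition, 120 × 0.8 = 96 are analysed, or 48 per arm. The t-test power at d = 0.5 is then 0.784.

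**3. Illustration at t12.** The article gives no workshop effect, no uptake and no expected effect at two years. All three are assumed here: a true d of 0.5 fully kept at two years, a workshop effect w (in SD, still present at t12), and attendance u.

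Observable d = 0.5 − w × u. Power is from the noncentral t distribution with noncentrality d × √(48/2), 94 degrees of freedom and one-sided .05.

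| w | u | w × u | Observable d | Power, 48 per arm |
|---|---|---|---|---|
| 0 | any | 0 | 0.50 | 0.784 |
| 0.1 | 50% | 0.05 | 0.45 | 0.707 |
| 0.2 | 80% | 0.16 | 0.34 | 0.504 |
| 0.3 | 80% | 0.24 | 0.26 | 0.352 |

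The first row also describes a workshop held after t12, or one that leaves no lasting effect on FIS.

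**The case against.** The strongest reply is that this may be harmless. The article gives the workshop's topic but not its length, content or uptake. Both arms already attend a workshop-based practicum on relational and communicative skills, and both go through two further years of ordinary education before t12. The Introduction itself argues that didactic methods alone do little to change behaviour. A compensation workshop could add almost nothing that survives two years, and a lasting effect of 0.3 SD would be 60% of the effect assumed for the whole apprenticeship. The Sample size section does not tie its power statement to t12, and the trial calls itself exploratory.

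Much of this stands. A reader might infer that the two-year result is certainly biased toward no effect. The article does not support that: the bias requires a workshop effect that lasts, and the power figures above illustrate a mechanism rather than predict a loss. Nor is the comparison invalid. It remains a randomised contrast, but of something other than what the article names.

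A reader might also infer that the trial could never distinguish fading from catch-up. That too goes too far. FIS is rated at three time points in both arms, by raters blind to condition and time, so a decline among apprentices or a rise among controls would be informative. The intervention arm's own course from t11 to t12 is not touched by the workshop. This evidence is only partial: ordinary training also moves scores, and the within-arm change has no untreated comparator. The analysis that the article describes is between conditions.

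The reply does not restore the t12 contrast claimed under Study design and under Strengths and limitations. Nor can the sponsor comfortably assume a zero workshop effect, since the fifth research question itself supposes that early training in interpersonal skills can last two years.

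**Conclusion.** The asymmetry is certain from the text. At two years the between-condition comparison estimates training-as-usual plus apprenticeship against training-as-usual plus a workshop offer.

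The direction of any resulting bias is conditional: toward zero, as an estimate of the apprenticeship effect, if the workshop improves FIS or self-efficacy and some of that remains at t12. The magnitude is unknown. The range shown rests wholly on assumed values for the two-year effect, the workshop effect and attendance.

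The first research question, answered at t11, is unaffected because controls are offered the workshop only after completing those measures. The point should be fixed, and its reach is limited to the two-year outcomes.

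**What to change.** **Controls not yet offered the workshop.** Hold it after the t12 assessment, or replace it with compensation unrelated to interpersonal skills. Either choice restores the intended contrast at t12 and needs no extra participants. The cost is a somewhat weaker incentive for controls: the workshop is there to help recruitment and reward participation, and delaying it or changing its topic could also affect control-arm retention to t12.

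**Cohorts already offered it.** Recruitment began in September 2021 (Status and timeline), so there may be some. For these:

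- Record who attended, where this can still be established, and report it descriptively. Do not adjust for attendance, which arises after randomisation.
- Report the t12 contrast as apprenticeship versus training-as-usual plus workshop offer, and add this to the limitations.
- Do not interpret a small t12 difference as loss of the apprenticeship gain. Show both arms' t11-to-t12 trajectories beside it, labelled as partial evidence.

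These steps cost an attendance list and a few sentences of reporting.
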